### Exposures

Data on all primary care prescriptions from 90 days prior to pregnancy through to the end of pregnancy, including those that have been initiated in secondary care and continued in primary care, will be extracted. Prescribing patterns will be assessed throughout pregnancy and by trimester and 90 days prior to pregnancy start. Trimesters will be defined as per the CPRD pregnancy register. Medications will be classified using British National Formulary (BNF) and Anatomical Therapeutic Chemical (ATC) systems.

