## Statistical analysis

### Objective 1: Descriptive analysis

Individual medications will be grouped into summary categories broadly based on BNF chapter and section (S1 Table) [23]. Binary variables will be created for whether a medication from each of the categories was prescribed at any time during the pregnancy, each trimester of pregnancy individually, and for the three-month period prior to the start of pregnancy. Rates of prescribing of each medication category will be calculated per 1000 pregnancies.

To look at trends over time, rates of prescribing will be calculated for each year separately, with a pregnancy assigned to a single year based on the start date of the pregnancy.

Factors influencing the prevalence of prescribing of medication groups during pregnancy will be investigated by modelling whether a prescription was issued for a given medication group during pregnancy, using multivariable logistic regression models including variables such as maternal age, ethnicity, geographical region, deprivation, and comorbidities.

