### Objective 2: Signal detection

Adverse outcomes will be defined as above. Exposures will be prescriptions of individual active ingredients of medications. The estimated dates of pregnancy will be used to identify any medications prescribed in the three months prior to pregnancy or during pregnancy, and analyses will be run for each trimester separately as well as for the three-month period prior to pregnancy.

We will apply standard Bayesian signal detection models using the Information Component (IC) [24–26]. This method is based on comparing the frequency of occurrence of the outcome of interest in mothers prescribed the medication of interest compared to the frequency of occurrence of the outcome of interest in mothers not prescribed the medication of interest for each medication/outcome pair. IC values that are positive indicate that the outcome and prescribed medication occur more frequently together than would be expected due to chance if both events were independent. In brief the observed counts (a,b,c,d from a two-by-two table) are assumed to have a Multinomial distribution (pa,pb,pc,pd,n). With a Dirichlet prior distribution for pa pb pc and pd the corresponding posterior distribution is also a Dirichlet distribution. Assuming an uninformative prior likelihood, 100,000 random samples from the proposed posterior Dirichlet distribution can be generated and the median IC with its 95% credible intervals obtained [27]. Pairs with a positive lower 95% credible interval have sufficient evidence that they are occurring more frequently than would be expected due to chance and are classified as signals.

Our new method of hierarchical modelling will then use these results to identify groups in the data using bi-clustering techniques. For this method, pairs with a positive lower 90% credible interval using the IC are considered ‘potential signals’. A group is defined as containing all medication/outcome pairs where all medications in the group have a potential signal with the same outcomes in the group. Medications with similar pharmacological properties are likely to be in the same groups, but the actual group membership is determined purely by the data. These groups will then be used to calculate an observed to expected ratio, adjusted for groupings, for each medication/outcome pair.

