### Limitations

As an observational study based on routinely collected data, there is potential for misclassification of exposures, outcomes, and of pregnancy status. The CPRD pregnancy register is based on an algorithm that searches for clinical codes likely to indicate pregnancy and generates estimated gestational dates from this. Some of the clinical codes used may generate false pregnancies, as has been highlighted in analyses of valproate use where the use of codes such as ‘*Advice on risk harm to fetus from maternl medictn dur preg’* are used when a patient is not pregnant [28]. To minimise the impact of this, where a pregnancy is based on a single code, the appropriateness of including these pregnancies will be reviewed based on the original codes used. Where HES linkage is available, we will also use this to triangulate whether a pregnancy is a true pregnancy, pregnancy outcome, and estimated gestation dates [17].

There is also the potential for residual confounding, particularly confounding by indication, which may not be possible to fully address through statistical adjustment. Prescription records indicate medications issued in primary care but we do not have data on whether prescriptions were collected and taken, so exposure misclassification must be considered.

Outcome misclassification is also possible due to imperfect coding, variation in recording practices, and limited clinical detail for some outcomes. Although signal detection methods are designed for hypothesis generation rather than causal inference, there remains a risk of identifying spurious associations arising from multiple testing or correlated exposures and outcomes. For these reasons, signals identified in this study will be interpreted cautiously and used primarily to prioritise medications for further investigation rather than to draw any definitive conclusions about causality.

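### Exposure windows follow the prescribing date, so women whose pre-pregnancy supply runs into early pregnancy without a first-trimester re-issue are counted as unexposed in the first-trimester table

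*Protocol article*

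**What the plan says.** All references are to the protocol article.

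- Exposures: the extract covers "Data on all primary care prescriptions from 90 days prior to pregnancy through to the end of pregnancy".
- Objective 2 defines exposure as an event, not a period of supply: "Exposures will be prescriptions of individual active ingredients of medications".
- Objective 2 places that event in time by when the drug was prescribed: "The estimated dates of pregnancy will be used to identify any medications prescribed in the three months prior to pregnancy or during pregnancy". It adds that "analyses will be run for each trimester separately as well as for the three-month period prior to pregnancy".
- The comparator is "the frequency of occurrence of the outcome of interest in mothers not prescribed the medication of interest for each medication/outcome pair".
- Objective 1 works on the same basis, "modelling whether a prescription was issued for a given medication group during pregnancy".
- A signal is declared on the lower credible limit of the Information Component (IC): "Pairs with a positive lower 95% credible interval have sufficient evidence that they are occurring more frequently than would be expected due to chance".
- Limitations accepts one form of exposure error: "we do not have data on whether prescriptions were collected and taken, so exposure misclassification must be considered".

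The article does not mention quantity, days' supply, or a prescription from one window running into the next.

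**The concern.** Take a woman issued eight weeks' supply two weeks before pregnancy and nothing afterwards. Her supply covers the first six weeks of pregnancy. Under the written rule she is exposed in the pre-pregnancy table and unexposed in the first-trimester table. Users who stop once they recognise the pregnancy are in this position, and so are users whose pregnancy ends before the next issue is due. Both are early exposures of the kind a pregnancy safety screen looks for, and congenital anomaly and miscarriage are both on the outcome list.

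The error admitted under Limitations runs the other way: it concerns women counted as exposed who may not have taken the drug. Supply carried into pregnancy produces women counted as unexposed who may well have taken it.

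Two things are at stake in the first-trimester table: exposed cases, on which the credible limit depends, and, for miscarriage, the direction of the estimate.

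**Working it through.** The article gives no figure on this point, so there is none to reproduce. All inputs below are assumptions for illustration except the 90-day look-back and the signal rule.

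**1. Who is missed.** Take a regular user re-issued every L days, with issue dates uniform over the interval, who stops ordering on day R of pregnancy. Her first issue due after pregnancy start is uniform on 0 to L, and she is missed if it falls after R:

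share missed = max(0, 1 − R/L)

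| Stops at day R | L = 28 | L = 56 | L = 84 |
|---|---|---|---|
| 14 | 50% | 75% | 83% |
| 28 | 0% | 50% | 67% |
| 35 | 0% | 37.5% | 58% |
| 42 | 0% | 25% | 50% |

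These are shares of stoppers, not of all first-trimester users. Anyone re-issued within the trimester is classified correctly.

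**2. Are they lost from the screen?** A supply of at most 84 days that spans pregnancy start was issued within the preceding 84 days, hence inside the 90-day look-back. All these women are in the exposed row of the pre-pregnancy table. What that table lacks is separation from women whose supply had already ended.

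**3. Effect when missing is unrelated to outcome.** Assume 500,000 pregnancies, 2% baseline risk and true risk ratio (RR) 2. With use q and share m missed, the exposed risk stays at 0.04, and the unexposed risk becomes [(1 − q)(0.02) + qm(0.04)] / [(1 − q) + qm].

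- q = 5%, m = 30%: unexposed risk = (9,500 + 300)/482,500 = 0.02031, so observed RR = 1.97.
- q = 20%, m = 30%: (8,000 + 1,200)/430,000 = 0.02140, so observed RR = 1.87. With m = 50% it is 1.80.
- q = 0.2%: 2.00 to two decimals for m = 30% or 50%.

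Exposed cases fall by the full share m. The lower 95% limit of the IC, from 100,000 Dirichlet draws with an assumed prior of 0.5 per cell, was:

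| Use | All captured | 70% captured | 50% captured |
|---|---|---|---|
| 0.05% | +0.06 (10 cases) | −0.15 (7 cases) | −0.37 (5 cases) |
| 0.2% | +0.54 (40 cases) | +0.45 (28 cases) | +0.35 (20 cases) |

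The first-trimester table loses the signal only where it was marginal to begin with.

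**4. Miscarriage.** Here an early loss itself shortens the time for a re-issue. Assume regular users who do not stop, 1% use, 15% baseline risk, true RR 1.5, losses at day 42, and a first trimester long enough for every ongoing pregnancy to be re-issued. Per 100 exposed pregnancies there are 22.5 losses and 77.5 ongoing; per 9,900 unexposed there are 1,485 losses.

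- L = 56: 25% of exposed losses (5.625) move to the unexposed row. Exposed risk = 16.875/94.375 = 0.1788; unexposed risk = 1,490.625/9,905.625 = 0.1505; observed RR = 1.19.
- L = 84: 50% (11.25) move. 11.25/88.75 = 0.1268; 1,496.25/9,911.25 = 0.1510; observed RR = 0.84.
- L = 28: none move, and RR stays at 1.5.

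**5. What a combined window recovers.** Adding the last 28 days before pregnancy changes the share missed to max(0, 1 − (R + 28)/L). At R = 42 this is 0% for L = 56, so RR returns to 1.5. For L = 84 it is 1 − 70/84 = 16.7%: exposed risk = 18.75/96.25 = 0.1948, unexposed risk = 1,488.75/9,903.75 = 0.1503, observed RR = 1.30. The error shrinks but is not always removed.

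**The case against.** The strongest reply is that the windows are not mutually exclusive. As step 2 shows, every woman with a spanning supply of up to 84 days is exposed in the pre-pregnancy table, whether she later stops or continues. A reader might infer that early harm is split between two tables and could trigger a signal in neither. The documents do not support that: the exposures are all present in one table, and the dilution there has not been quantified. The signals lost in step 3 concern the first-trimester table alone.

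A second reply is that the percentages depend on chosen inputs. With 28-day supplies and stopping at day 35 to 42 nobody is missed, and the share of users who stop is unknown. This stands; the figures show a range and do not estimate the loss in this study.

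Third, a reader might conclude that a supply-overlap rule should replace the prescribing-date rule. That would be a trade-off. It would count women who stopped before pregnancy with supply left over as exposed, and for a rare drug false positives dilute more than false negatives. If an assumed 30% of the exposed row were truly unexposed, RR 2 would become 0.7 × 2 + 0.3 × 1 = 1.7, whereas missing 30% leaves it near 2. The article also gives no basis for a default duration where none is recorded.

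Fourth, the article condenses a separately approved protocol that may treat supply. That is possible. But the article positively defines exposure as a prescription placed by date, so the point does not rest on silence alone.

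**Conclusion.** The point holds in a limited form. Followed as written, the rule puts women with carried-over supply and no first-trimester re-issue in the unexposed row of the first-trimester analysis. The pre-pregnancy analysis counts them without separating them from women whose supply had ended. For most outcomes this costs exposed cases more than it biases the ratio: RR 2 stays near 2.0 for rare drugs and falls to about 1.8-1.9 at 20% use with 30-50% missed. Miscarriage is the more serious case, because the misclassification depends on the outcome. On the assumptions in step 4, a true RR of 1.5 appears as about 1.19 with 56-day and 0.84 with 84-day repeats, and is unaffected with 28-day repeats. All these sizes rest on assumed supply lengths, stopping or loss times, risks and prevalence of use. The rule does not remove these exposures from the screen as a whole, and women re-issued in the first trimester are not affected.

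**What to change.** Keep the prescribing-date rule as the primary definition. For congenital anomaly and miscarriage, add one sensitivity analysis in which a pregnancy is exposed if the drug was prescribed in the last 28 days before pregnancy or in the first trimester. Where quantity and directions are recorded, overlap of supply with the first trimester can be an optional further check. Add a sentence on carried-over supply to Limitations.

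The prescriptions needed fall within the 90-day look-back, and the combined window requires no duration data. The cost is one more set of tables for two outcome groups. Some women who stopped before pregnancy will be counted as exposed, so the result should be read beside the primary tables. It does not correct the same timing problem for women who first start a drug during the first trimester, and it only partly corrects it for supplies near 84 days.

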### Outcomes

Adverse outcomes will be identified using coded data from primary care, hospital admissions, and linked datasets. Outcomes will be grouped into maternal, fetal, and infant categories, based on the Core Data Elements for pregnancy pharmacovigilance developed by the European Network of Teratology Information Services and ConcePTION consortium [6,14,19] (Table 1).

**Table 1 pone.0349045.t001:** Outcome groups to be extracted from health records.

**Maternal**	Maternal medical conditions arising in pregnancy
	Maternal delivery complications
	Maternal post-partum complications
	Maternal death
**Fetal**	Molar pregnancy
	Ectopic pregnancy
	Miscarriage
	Premature delivery
	Congenital anomaly
	Stillbirth
**Infant**	Small-for-gestational-age at delivery
	Large-for-gestational-age at delivery
	Neonatal death
	Infant death
	Hospital admissions

The maternal medical conditions arising in pregnancy outcomes will include: gestational diabetes; hypertensive disorders of pregnancy; venous thrombotic episode; depression/anxiety/psychosis; pulmonary oedema; acute kidney injury; stroke; maternal infections; antepartum haemorrhage. The congenital anomaly outcome will include major congenital anomaly subgroups of heart, limb, kidney and urinary tract, digestive system, nervous system, abdominal wall, respiratory, and oro-facial clefts.

For our clinical outcomes, some of the relevant code lists have already been developed and will be accessed from code repositories and publications and reviewed by our clinical team, e.g., pre-eclampsia [20], stroke [21], congenital anomalies [22]. Some pregnancy related outcomes are also included in the pregnancy register data received from CPRD, e.g., stillbirth, miscarriage, ectopic pregnancy, molar pregnancy [15]. For outcomes with no appropriate published codelists, we will develop new code lists.

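### For maternal conditions that arise during pregnancy, the signal screen does not require the prescription to precede the outcome, so medicines prescribed because of the diagnosis can be flagged as signals

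*Protocol article*

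**What the plan says.** Three parts of the protocol article bear on this.

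- **Exposures** sets the extraction window: "Data on all primary care prescriptions from 90 days prior to pregnancy through to the end of pregnancy". The window is tied to the pregnancy, not to the date of any outcome.
- **Objective 2: Signal detection** defines exposure within it: "The estimated dates of pregnancy will be used to identify any medications prescribed in the three months prior to pregnancy or during pregnancy". The same sentence adds that "analyses will be run for each trimester separately as well as for the three-month period prior to pregnancy", which makes four windows. The Information Component (IC) rests on "comparing the frequency of occurrence of the outcome of interest in mothers prescribed the medication of interest" with the frequency in mothers not prescribed it. The signal rule is: "Pairs with a positive lower 95% credible interval have sufficient evidence". A looser rule, a lower 90% limit above zero, decides which pairs form the bi-clusters for the hierarchical model.
- **Outcomes** lists conditions that are diagnosed while these windows are open: "The maternal medical conditions arising in pregnancy outcomes will include: gestational diabetes; hypertensive disorders of pregnancy; venous thrombotic episode; depression/anxiety/psychosis", followed by others that include maternal infections and antepartum haemorrhage.

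The Abstract says that confounders are not dealt with at the screening stage. Under Objective 3, signals are later annotated, with one category for known indication effects, and clinicians discuss confounding by indication. Neither these steps nor the Limitations mention the order of prescription and outcome.

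**The concern.** Followed as written, a woman who develops a new condition in a given trimester and is then prescribed something in that trimester or a later one is an exposed case. This differs from the unadjusted confounding that the authors openly accept at this stage, because here the outcome brings about the exposure. Excluding women who had the condition before pregnancy would not remove it, since these cases are new in pregnancy.

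Two kinds of medicine are affected: treatments of the condition itself, and non-specific medicines prescribed more often because a complicated pregnancy is seen more often. Both can be declared signals. Treatments of one complication share the same outcome, and shared outcomes are what defines a group, so they can also form bi-clusters and shift the group means. The estimated size then enters prioritisation as a population attributable risk, commonly prescribed medicines are favoured, and only three signals get a cohort study.

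**Working it through.** The article gives no sample size, event count or expected number of signals, so there is no figure of its own to reproduce. All rates below are assumptions.

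**1. Observed/expected ratio with no causal effect.** Let *p* be the outcome risk, *c* the share of cases prescribed the medicine and *n* the share of non-cases. Then O/E = *c* / [*p c* + (1 − *p*) *n*]. Take *p* = 5%, with all the excess among cases prescribed after diagnosis.

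| Medicine | *n* | *c* | O/E |
|---|---|---|---|
| Usual treatment | 0.5% | 30% | 0.30 / (0.015 + 0.00475) = 15.2 |
| Non-specific, common | 10% | 15% | 0.15 / (0.0075 + 0.095) = 1.46 |
| Non-specific, common | 10% | 20% | 0.20 / (0.010 + 0.095) = 1.90 |
| Non-specific, less common | 2% | 6% | 0.06 / (0.003 + 0.019) = 2.73 |

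**2. The plan's own screen.** The article says that "100,000 random samples from the proposed posterior Dirichlet distribution can be generated" under an uninformative prior. I read this as Dirichlet(1,1,1,1) and took IC = log2[pa / ((pa + pb)(pa + pc))]. Tables were set at expected counts for a medicine with no effect, background use *q*, and a share *u* of the remaining cases prescribed it after diagnosis, so *c* = *q* + (1 − *q*)*u*. Ranges: 100,000 and 500,000 pregnancies; outcome risk 1%, 5% and 10%; *q* from 0.1% to 5%; *u* of 0, 1%, 5% and 30%. A single exposure window was modelled.

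- *Example* (500,000 pregnancies, risk 5%, *q* = 0.5%, *u* = 30%): counts 7,588, 2,375, 17,412 and 472,625; O/E 15.23; IC 3.93 (3.91 to 3.95).
- *Smallest u that is flagged*, with *q* from 0.5% to 5%: about 0.1% to 0.7% of cases at 500,000 pregnancies, and 0.2% to 1.5% at 100,000.
- *u = 30%*, 500,000 pregnancies: median IC 2.09 to 6.23 (O/E 4.3 to 75). A genuine relative risk of 3 gives 1.53 to 1.58 (*q* of 0.5% or 2%).
- *u = 5%, q = 0.5%*, 500,000 pregnancies: IC 2.46 to 3.32, still above a relative risk of 3.
- *u = 5%, q = 5%*, 500,000 pregnancies: IC 0.83 to 0.95. This is about the level of a genuine relative risk of 2, which gives 0.97 to 1.01 at *q* of 0.5% or 2%, and log2(2/1.05) = 0.93 at *q* = 5%. The pair is flagged but not at the top.

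**3. With post-diagnosis prescriptions removed (*u* = 0).** The IC is near zero and its interval covers zero in every scenario. In the example it is 0.01 (−0.25 to 0.24).

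**4. Effect on prioritisation.** The population attributable share is *c*(1 − 1/RR). For *n* = 10% and *c* = 15%, RR = (0.0075/0.1025) / (0.0425/0.8975) = 1.545, and the share is 0.15 × (1 − 1/1.545) = 5%. For *c* = 20%, RR = (0.010/0.105) / (0.040/0.895) = 2.13, and the share is 0.20 × (1 − 1/2.13) = 11%. Both belong to a medicine with no effect.

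**The case against.** - **The windows already help.** Every condition that arises in pregnancy follows the pre-pregnancy window, and a condition that starts in a later trimester follows the earlier ones. This stands. A reader might infer that the screen says nothing about prescribing before onset; the four separate analyses contradict that. The problem is confined to the trimester of onset and later ones.
- **Most outcome groups are not exposed to it.** Extraction stops at the end of pregnancy. Miscarriage, stillbirth, premature delivery, post-partum complications and infant outcomes come at or after that point. This largely stands, although antenatal detection of a fetal problem could still precede a prescription.
- **Later steps filter signals.** The annotation will catch textbook treatments, clinicians review confounding by indication, the three cohort studies can set their own time order, and the Limitations restrict signals to prioritisation. This stands for obvious treatments. But the filter comes after pairs have been flagged and grouped, and a non-specific medicine has no recognised indication for the label to find.
- **The article is condensed.** The approved protocol is not shown and may contain a date rule. That is possible, and the article's silence does not show that the authors intend to count post-diagnosis prescriptions. The point rests on what the article does fix: windows anchored on pregnancy dates, outcomes inside them, and a co-occurrence table.

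**Conclusion.** The concern holds for maternal conditions arising during pregnancy, in the analyses of the trimester of onset and later trimesters. There, a medicine with no effect can be flagged and can shape the bi-clusters. Under the assumed rates its O/E is about 15 for a usual treatment and about 1.5 to 2.7 for non-specific medicines, and in a database of 500,000 pregnancies well under 1% of cases need receive it after diagnosis for it to be flagged.

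A reader might go further and conclude that such pairs will be the strongest signals or dominate the ranking. The documents do not support that: they give no uptake, background use or prevalence. In the calculations it was true at 30% uptake, but not for a commonly used medicine given to few cases. Nor did the calculations model how the bias differs across the four windows.

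**What to change.** For outcomes dated within pregnancy, build each window's two-by-two table at a landmark at the end of that exposure window:

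- include only pregnancies that are ongoing and free of the outcome at the landmark;
- classify exposure from prescriptions up to the landmark;
- count only outcomes first recorded after it.

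Use these tables for the IC, for the 90% rule that forms the groups, and for the hierarchical model. The four-cell multinomial and Dirichlet model stays as it is, and the rule can be fixed before signals are generated, which the Timeline expects by autumn 2026.

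The cost is some reprogramming with dates already held, and a loss of information. Onsets within the same window are dropped and counts fall. The loss is greatest for third-trimester exposure: that window runs to the end of pregnancy, so few antenatal onsets remain after its landmark. Acute effects within a window would need a separate sensitivity analysis, for example gestational-week person-time. That does not fit the four-cell table and needs its own observed/expected likelihood, so it should be optional and not replace the main screen. The rule also relies on recorded dates approximating onset, and the Limitations already warn of estimated gestation dates and imperfect outcome coding.
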